### Power calculation

In each of the seven sites, 120 participants will be included in the intervention group and 120 participants in the control group. Assuming a 20% participant loss to follow-up between *T*_0_ and *T*_1_ (e.g. due to disability, rehousing, mortality, study withdrawal), we expect to get complete data from 672 participants in the intervention group and 672 participants in the control group of all sites at follow-up; in total *n* = 1344 study participants. We assume equal standard deviations in the intervention group and the control group, alpha of 0.05 and power of 0.80. Thus, given seven participating study sites each with an intervention group and control group, we applied a correction factor to account for the cluster design, assuming an average cluster size of 96 older citizens (1344/14) and an intra-class correlation coefficient of 0.02. For this expected overall sample size and assumptions, regarding the continuous outcome measures, a difference of 0.23 SD between the intervention and the control group can be detected at follow-up. This means that both at the European level and within each individual site, small differences regarding the outcomes in the intervention group compared to the control group can be shown [67].

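### The stated detectable difference of 0.23 SD needs an undeclared one-sided 5% test; read two-sided, the same inputs give 0.26 SD, or about 70% power at 0.23 SD

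*Protocol article*

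**What the plan says.** The Power calculation section fixes the recruitment: "In each of the seven sites, 120 participants will be included in the intervention group and 120 participants in the control group". With seven sites that is 840 per arm. After the assumed 20% loss between baseline and 12 months, the section bases its result on "672 participants in the intervention group and 672 participants in the control group of all sites at follow-up", 1344 in all.

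The statistical inputs are given as follows: "We assume equal standard deviations in the intervention group and the control group, alpha of 0.05 and power of 0.80". The clustering correction is made by "assuming an average cluster size of 96 older citizens (1344/14) and an intra-class correlation coefficient of 0.02". From these the section concludes that "a difference of 0.23 SD between the intervention and the control group can be detected at follow-up".

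Sidedness is not mentioned there. Under Data management and analyses, results with a P-value of 0.05 or lower count as significant, again without sidedness. That section plans multilevel linear and logistic regression and subgroup analyses by interaction tests. The Hypotheses section expects better results in the intervention group but does not announce a one-sided test.

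**The concern.** A difference expressed in SD units, with the sample size, cluster size, intra-class correlation, alpha and power all printed, can be checked directly. Under the usual two-sided reading of alpha 0.05, the check does not return the printed value. It returns a larger one, so the article's figure is the more favourable of the two.

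This is the article's only power statement, and it covers the main outcome, PROMIS-10 health-related quality of life. A reader facing a null result would take it that a true difference of 0.23 SD had an 80% chance of being found. If the test is two-sided, the calculation supports only about 70% for that difference. The risk of missing it is then about 30% instead of 20%.

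**Working it through.** **Inputs, all from the Power calculation section**

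- Completers per arm: 7 × 120 = 840 enrolled; 840 × 0.80 = 672.
- Average cluster size: 1344/14 = 96.
- Intra-class correlation: 0.02.
- Alpha 0.05, power 0.80, equal SDs (SD = 1, since the effect is in SD units).
- Not given: one- or two-sided alpha.

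**Common steps (normal approximation)**

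- Design effect = 1 + (96 − 1) × 0.02 = 2.90.
- Effective n per arm = 672/2.90 = 231.7.
- Standard error of the difference = √(2/231.7) = 0.0929 SD.
- Detectable difference = (z for alpha + z for power) × 0.0929.
- Power at 0.23 SD = Φ(0.23/0.0929 − z for alpha).

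**Reproducing the printed figure: one-sided alpha 0.05**

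- Detectable difference = (1.645 + 0.842) × 0.0929 = 0.231 SD.
- Power at 0.23 SD = Φ(2.476 − 1.645) = 79.7%.

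This matches the article with no other input changed.

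**Two-sided alpha 0.05**

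- Detectable difference = (1.960 + 0.842) × 0.0929 = 0.260 SD.
- Power at 0.23 SD = Φ(2.476 − 1.960) = 69.7%.
- 0.260/0.23 = 1.13, so the detectable difference is 13% larger than printed.
- For scale, 80% power at 0.23 SD would need 297 × 2.90 = 861 analysed per arm, with the design effect held at 2.90.

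**Other ways to arrive near 0.23 with a two-sided test**

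| Route | Result | Agrees with the text? |
|---|---|---|
| 840 per arm with design effect 2.90: effective n 289.7 | 0.233 SD | No; the text says the figure is for the sample after loss |
| 840 per arm with its own cluster size of 120: design effect 3.38, effective n 248.5 | 0.251 SD | No, and it does not give 0.23 |
| 672 per arm with an intra-class correlation of about 0.013 | 0.23 SD | No; the text says 0.02 |

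Of the routes checked, only the one-sided test gives 0.23 SD without contradicting a printed input.

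**The case against.** The strongest reply is that two-sidedness is not a printed input. The text says only "alpha of 0.05 and power of 0.80", and a one-sided 5% test reproduces 0.23 SD from everything that is printed. The hypotheses are worded in one direction, so a one-sided calculation cannot be excluded. This stands against one tempting reading, that 0.23 SD cannot be derived from the stated inputs. It can be, and the point has to be put conditionally.

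It does not leave the text adequate as written. A one-sided 5% test departs from convention and has to be declared. The article applies one unqualified 0.05 threshold to regression models and to interaction tests, where two-sided testing is the default. A directional hypothesis is not a declaration of a one-sided test. The match does not show intent either, because ignoring the loss to follow-up gives nearly the same number.

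A reader might also infer that the trial itself has only 70% power. The documents do not support that. The 70% belongs to the comparison at follow-up that the Power calculation section describes. The planned multilevel models use the measurements at baseline, 12 and 18 months, and adjusting for baseline could improve precision. As an assumption, a baseline correlation of about 0.47 that reduced variance equally at both levels would close the gap between 0.26 and 0.23 SD. The article's calculation claims no such gain, so this does not repair the printed figure.

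A reader might further want to enlarge the detectable difference because there are only 14 clusters. The article names no small-sample reference distribution or degrees of freedom. Each site contributes both an intervention and a control group, and may include several practices, centres or hospitals. Any such figure would rest on choices the document does not make, so none is used here.

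Finally, the sample size is not presented as derived from 0.23 SD. The figure is an output of a fixed recruitment target, and no stated target effect depends on it. This stands, and it limits how serious the point is.

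**Conclusion.** The point holds in conditional form. With design effect 2.90 and 672 completers per arm, 0.23 SD is the detectable difference for a one-sided 5% test that the article does not declare. On the conventional two-sided reading of both the power calculation and the analysis threshold, it is 0.26 SD, and power at 0.23 SD is 69.7%.

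This rests on the article's own cluster size, intra-class correlation and loss to follow-up, on the normal approximation, and on a comparison at follow-up without baseline adjustment. A separate statistical analysis plan, not available here, may state the sidedness. If it says two-sided, the printed figure is wrong; if one-sided, the article omits a design choice that its figure depends on.

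The figure should be corrected because it is the only power statement for the main outcome. It does not show that the study is too small, and it is not a defect that must be resolved before the study can proceed.

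**What to change.** In the Power calculation section, state that the test is two-sided and give the detectable difference as 0.26 SD (672 per arm, design effect 2.90, 80% power). Alternatively, keep 0.23 SD and state power of about 70%. Add the word two-sided to the significance rule under Data management and analyses, so that the calculation and the analysis use the same threshold.

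If a one-sided 5% test was really intended, declare it in both sections; 0.23 SD can then stay.

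The cost is one sentence in the power section and a word in the analysis section. Recruitment and design do not change. The only downside is a slightly less favourable stated figure.

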### Data management and analyses

A data management plan is being developed as part of the ValueCare project and will be updated throughout the project. The document describes the data life cycle, from definition to reuse after the project. It follows a privacy-by-design approach and includes procedures for ensuring a high-quality data standard, in compliance with the FAIR principles. As the project will collect health-related data, special attention is attributed to the role of each partner in terms of controllers and processors, and to the organisational and technical measures to be put in place to ensure General Data Protection Regulation (GDPR) compliance. In addition, the risks associated to data processing will be defined in the Data Protection Impact Assessment (art. 35 GDPR) to be evaluated together with the Controllers’ Data Protection Officers. Erasmus University Medical Center is responsible for the data management, analysis and reporting.

Descriptive statistics will be used to describe participant characteristics in each site and in the total study population. Differences between *T*_0_, *T*_1_ and *T*_2_ measurements are evaluated using multilevel linear regression analyses for continuous outcome variables and multilevel logistic regression analyses for dichotomous outcome variables. We will perform subgroup analyses through formal interaction tests including those variables that are likely to influence the effect of the intervention itself, such as age, sex, living situation, education level and the baseline status of the outcome variable. Statistical analyses are repeated for each site separately. We consider a P-value of 0.05 or lower to be statistically significant.

To assess changes in implementation outcome measures from baseline (*T*_0_) to follow-up (*T*_1,_
*T*_2_) *t* tests for continuous measures and chi square for categorical variables will be used. Qualitative analysis will be performed on the focus group data. Focus groups will be digitally recorded and transcribed. The data will be managed using N-Vivo 10 software. The data will be analysed using thematic content analysis.

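### The 0.23 SD detectable difference holds for the pooled sample only; a single site with 96 completers per arm detects about 0.40 SD ignoring clustering, so the site-level power claim is wrong.

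*Protocol article*

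**What the plan says.** The Power calculation section states that in each of the seven sites "120 participants will be included in the intervention group and 120 participants in the control group". After 20% loss it expects "672 participants in the intervention group and 672 participants in the control group of all sites at follow-up". It then applies a design-effect correction: "given seven participating study sites each with an intervention group and control group, we applied a correction factor to account for the cluster design". The average cluster size is 96 (1344/14) and the ICC is 0.02. For this overall sample it reports a detectable difference of 0.23 SD. The closing sentence presents as a consequence that "both at the European level and within each individual site, small differences regarding the outcomes" can be shown. No separate site-level calculation is given.

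Data management and analyses specifies multilevel linear and logistic models, sets significance at P of 0.05 or lower, and adds: "Statistical analyses are repeated for each site separately".

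The Study design section says that GP practices, community centres and hospitals are chosen as intervention and control sites in each country. These are plurals, and no number per arm is given.

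**The concern.** A detectable difference computed from 672 per arm cannot carry over unchanged to a site with one seventh of that number. The claim matters because the site-level analyses are actually planned, and because the target groups differ by site (Table 2), so readers will look at single-site results. If a site is described as able to show small differences, a non-significant result there may be taken as evidence of no benefit, when the chance of detecting such a difference was low.

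A second, conditional issue concerns clustering. The power section counts 14 clusters, which is one intervention and one control cluster per site. On that count a site-level comparison sets one cluster against one other. The between-cluster variance then cannot be estimated within the site, and a significant result could reflect a difference between centres rather than the intervention.

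**Working it through.** **Inputs, all from Power calculation**
- Enrolment of 120 per arm per site, and "Assuming a 20% participant loss to follow-up between" baseline and 12 months: 120 × 0.8 = 96 completers per arm per site, and 7 × 96 = 672 per arm overall.
- "alpha of 0.05 and power of 0.80"; sidedness is not stated.
- "We assume equal standard deviations in the intervention group and the control group", so effects are in SD units.
- Cluster size 96 and ICC 0.02: design effect DE = 1 + (96 − 1) × 0.02 = 2.90.

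**Formula** (two means, normal approximation): detectable difference = (z_alpha + z_power) × √(2 × DE / n per arm). The multiplier is 1.960 + 0.842 = 2.802 two-sided and 1.645 + 0.842 = 2.487 one-sided.

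**Step 1. The article's own figure (n = 672, DE = 2.90)**
- One-sided: 2.487 × √(5.8/672) = 0.231 SD, which matches 0.23.
- Two-sided: 2.802 × √(5.8/672) = 0.260 SD, which does not match.
- Two-sided with the pre-dropout 840 per arm (7 × 120): 2.802 × √(5.8/840) = 0.233 SD, which also rounds to 0.23.

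The figure is therefore reproducible for the pooled sample, but the text does not settle which route was used. Both sidedness options are carried forward.

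**Step 2. The same formula for one site (n = 96 per arm)**

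| | DE = 1 | DE = 2.90 |
|---|---|---|
| Two-sided | 2.802 × √(2/96) = 0.404 SD | 2.802 × √(5.8/96) = 0.689 SD |
| One-sided | 2.487 × √(2/96) = 0.359 SD | 2.487 × √(5.8/96) = 0.611 SD |

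**Step 3. Power in one site at 0.23 SD, two-sided**
- No clustering: standard error √(2/96) = 0.144; Φ(0.23/0.144 − 1.96) ≈ 36%.
- DE 2.90: standard error √(5.8/96) = 0.246; Φ(0.23/0.246 − 1.96) ≈ 15%.

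**Step 4. What 0.23 SD would need in one site**
- Sample size without clustering, two-sided: 2 × (2.802/0.23)² ≈ 297 per arm, against 96 expected.
- Baseline adjustment multiplies the variance by 1 − r². The correlation r is not in the article. For assumed r of 0.5 to 0.7, the two-sided unclustered figure is 0.35 to 0.29 SD. Reaching 0.23 SD needs 1 − r² = (0.23/2.802)² × 48 = 0.32, so r ≈ 0.82, with no clustering. One-sided, 1 − r² = (0.23/2.487)² × 48 = 0.41, so r ≈ 0.77.
- Several units per arm: with an assumed 2 to 10 equal units per arm and ICC 0.02, cluster sizes are 48 to 9.6, DE is 1.94 to 1.17, and the two-sided figure is 0.56 to 0.44 SD.

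**Step 5. Site-level test if there is one cluster per arm**
A follow-up-only test that ignores clustering understates the standard error by √2.90 = 1.70. Its true two-sided type I error is 2 × (1 − Φ(1.96/1.70)) ≈ 25% at ICC 0.02. At assumed ICCs of 0.005, 0.01 and 0.05 it is about 11%, 16% and 41%.

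**The case against.** Four arguments can be made for the article.

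*The word small is not given a number.* A difference of 0.36 to 0.40 SD might still be called small. But the sentence is presented as following from the 0.23 SD just derived, so that is the only size it can refer to. With the article's own clustering allowance the site figure is 0.61 to 0.69 SD.

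*0.40 SD is not a floor.* This stands. A reader might take it as the best a site can do, but a one-sided test gives 0.36 SD, and the planned models use all three time points, so baseline information could lower it further. One-sided power at 0.23 SD without clustering is Φ(1.59 − 1.645) ≈ 48%. With assumed baseline correlations of 0.5 to 0.7, two-sided power is about 45% to 61%. None of these reaches 80%.

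*One cluster per arm is a planning simplification.* This also stands. A reader might infer that the site-level P-values are invalid. The documents do not establish that. Study design allows several practices, centres or hospitals per arm, and the analysis section does not say that the site-level repeats ignore clustering. Leaving the model levels to a fuller document is normal for an article.

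*The error rates are conditional.* The 25% requires one cluster per arm, an unadjusted follow-up-only test, and the whole ICC of 0.02 acting between two groups in the same site. Any between-country part of that ICC cancels within a site, and the article does not give the split. The same caution applies to the site-level figures that use DE 2.90. Compounding the 25% over seven sites (1 − 0.75⁷ ≈ 87%) would add the assumption that every site effect is null. It should not be quoted as a property of this trial.

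**Conclusion.** The site-level half of the power statement is wrong on the article's own inputs. With 96 completers per arm, the 80%-power detectable difference for an unadjusted follow-up comparison is 0.40 SD two-sided or 0.36 SD one-sided ignoring clustering, and 0.69 or 0.61 SD if the stated design effect applies in full within a site. No variant examined brings a site to 0.23 SD unless clustering is absent and the baseline correlation is high (about 0.82 two-sided, 0.77 one-sided).

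The confounding of intervention with cluster in the site-level tests follows only if the count of 14 clusters describes the real design. What the documents do show is that Power calculation and Study design leave the number of clusters per arm unclear. Nothing in this point affects the pooled comparison or the planned sample size.

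**What to change.** - In Power calculation, confine the closing sentence to the pooled analysis. Alternatively, add the site-level detectable difference with its sidedness and clustering assumption, for example 0.40 SD two-sided ignoring clustering and 0.69 SD with DE 2.90.
- Reconcile the cluster definition in Power calculation with the units described in Study design, and state how many units per arm each site has.
- In Data management and analyses, assess differences between sites through a group-by-site interaction in the pooled model, and report site estimates with confidence intervals as descriptive. If there is one cluster per arm in each site, say that site estimates and the interaction also contain the cluster differences.

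The cost is a few sentences and a less favourable stated figure at site level. Enrolment and data collection do not change.

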### Data management and analyses

A data management plan is being developed as part of the ValueCare project and will be updated throughout the project. The document describes the data life cycle, from definition to reuse after the project. It follows a privacy-by-design approach and includes procedures for ensuring a high-quality data standard, in compliance with the FAIR principles. As the project will collect health-related data, special attention is attributed to the role of each partner in terms of controllers and processors, and to the organisational and technical measures to be put in place to ensure General Data Protection Regulation (GDPR) compliance. In addition, the risks associated to data processing will be defined in the Data Protection Impact Assessment (art. 35 GDPR) to be evaluated together with the Controllers’ Data Protection Officers. Erasmus University Medical Center is responsible for the data management, analysis and reporting.

Descriptive statistics will be used to describe participant characteristics in each site and in the total study population. Differences between *T*_0_, *T*_1_ and *T*_2_ measurements are evaluated using multilevel linear regression analyses for continuous outcome variables and multilevel logistic regression analyses for dichotomous outcome variables. We will perform subgroup analyses through formal interaction tests including those variables that are likely to influence the effect of the intervention itself, such as age, sex, living situation, education level and the baseline status of the outcome variable. Statistical analyses are repeated for each site separately. We consider a P-value of 0.05 or lower to be statistically significant.

To assess changes in implementation outcome measures from baseline (*T*_0_) to follow-up (*T*_1,_
*T*_2_) *t* tests for continuous measures and chi square for categorical variables will be used. Qualitative analysis will be performed on the focus group data. Focus groups will be digitally recorded and transcribed. The data will be managed using N-Vivo 10 software. The data will be analysed using thematic content analysis.

Using the baseline measurement as control group, a preliminary cost-effectiveness analysis will be performed from a societal and healthcare perspective. The healthcare costs per individual participant will be calculated by multiplying resource use (e.g. doctor appointments, hospital admissions) with corresponding unit prices. The results from the iPCQ are used to determine productivity losses for individual participants (lost productivity at paid work due to absenteeism and lost productivity at unpaid work). Information from the EQ-5D-5L will be used to calculate utility values.

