**Methods:**

A pre-post controlled study design including three time points (baseline, post-intervention after 12 months, and follow-up after 18 months) and two groups (intervention and control group) will be utilised. In each site, (net) 240 older people (120 in the intervention group and 120 in the control group), 50–70 informal caregivers (e.g. relatives, friends), and 30–40 health and social care practitioners will be invited to participate and provide informed consent. Self-reported outcomes will be measured in multiple domains; for older people: health, wellbeing, quality of life, lifestyle behaviour, and health and social care use; for informal caregivers and health and social care practitioners: wellbeing, perceived burden and (job) satisfaction. In addition, implementation outcomes will be measured in terms of acceptability, appropriateness, feasibility, fidelity, and costs. To evaluate differences in outcomes between the intervention and control group (multilevel) logistic and linear regression analyses will be used. Qualitative analysis will be performed on the focus group data.

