### Objectives

The aim of the study is to evaluate the ValueCare approach, using a pre-post controlled design, measuring the benefits for each one of the target groups (older people using health and social care services, their informal caregivers, and health and social care practitioners), and thus to be able to properly evaluate implementation outcomes. The specific objectives are:To compare the benefits of the ValueCare approach versus usual care for older people with regard to indicators of health, wellbeing, quality of life, lifestyle behaviour, and health and social care use.To evaluate the benefits of the ValueCare approach for older people’s caregivers (e.g. relatives, friends), and health and social care practitioners in terms of wellbeing, perceived burden and (job) satisfaction.To evaluate the acceptability, appropriateness, feasibility, fidelity, and costs of the ValueCare approach.

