## Methods/design

### Study design

The evaluation of ValueCare has a pre-post controlled design with an intervention group (using the ‘ValueCare approach’) and a control group (‘care as usual’). Measurements are taken at baseline (*T*_0_), after 12 months (*T*_1_; the end of the ‘ValueCare approach’ intervention period), and at 18 months (*T*_2_) [32, 34, 35]. In each of the seven European countries, intervention and control sites (GP practices, community centres for health and wellbeing, and hospitals) are chosen. Table 1 shows the timeline of enrolment, interventions and assessments for this study. Baseline data collection is scheduled to commence by the end of 2021.

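### The main effectiveness analysis is stated as a contrast between time points, not between groups, and the main comparison of non-randomised groups has no stated covariate adjustment

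*Protocol article*

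**What the plan says.** The only model statement for the effectiveness outcomes in the Methods is in Data management and analyses: "Differences between *T*_0_, *T*_1_ and *T*_2_ measurements are evaluated using multilevel linear regression analyses". Dichotomous outcomes get the logistic counterpart. The sentence contains neither a group term nor a group-by-time term.

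Elsewhere the question is a comparison of groups:

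- Abstract, Methods: "To evaluate differences in outcomes between the intervention and control group (multilevel) logistic and linear regression analyses will be used".
- Objectives, first objective: "To compare the benefits of the ValueCare approach versus usual care for older people".
- Hypotheses: older people receiving ValueCare are expected to do better than those receiving usual care.
- Power calculation: the detectable difference of 0.23 SD is defined between the two arms at follow-up.

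On allocation, Study design says "intervention and control sites (GP practices, community centres for health and wellbeing, and hospitals) are chosen". The article mentions no randomisation, matching, weighting or propensity method.

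On covariates, Data management and analyses says "We will perform subgroup analyses through formal interaction tests including those variables that are likely to influence the effect of the intervention itself", and gives as examples "such as age, sex, living situation, education level and the baseline status of the outcome variable". This is the only role these variables receive.

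**The concern.** Two things do not fit together.

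First, a difference between T0, T1 and T2 measures change over time. Without a group term it includes recovery and secular trend as well as any effect of the intervention. Some target groups are patients after a myocardial infarction or an ischaemic stroke, in whom change without any intervention effect is plausible.

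Second, once the contrast is read as intervention versus control, the groups may still differ at baseline because the sites were chosen. Interaction tests ask whether the effect varies across subgroups. They do not remove baseline differences from the main estimate. As written, the variables that could serve for adjustment have been given a different job.

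At stake is whether the headline estimate of a non-randomised study can be read as an effect of ValueCare.

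**Working it through.** **Step 1: the stated contrast against the question**

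| Place in the protocol article | Contrast |
|---|---|
| Abstract, Methods | intervention versus control |
| Objectives (first) | ValueCare versus usual care |
| Hypotheses | intervention versus control |
| Power calculation | intervention versus control at follow-up |
| Data management and analyses, model sentence | T0 versus T1 versus T2 |

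The model sentence is the one that differs. Before-after contrasts do occur elsewhere. The hypothesis in the section on caregiver and practitioner outcomes compares follow-up with baseline, and the preliminary cost-effectiveness analysis takes the baseline measurement as its comparator. The wording is therefore open to a real misreading.

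**Step 2: the plan's own figure**

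Inputs from Power calculation: 672 completers per arm, cluster size 96, intra-class correlation 0.02, "alpha of 0.05 and power of 0.80".

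- Design effect = 1 + (96 - 1) × 0.02 = 2.90.
- Standard error of the group difference, in SD units = √(2 × 2.90 / 672) = 0.0929.
- One-sided alpha: (1.645 + 0.842) × 0.0929 = 0.231 SD.
- Two-sided alpha: (1.960 + 0.842) × 0.0929 = 0.260 SD.

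The stated 0.23 SD is reproduced with a one-sided alpha on the stated completers. Sidedness is not given, there or in "We consider a P-value of 0.05 or lower to be statistically significant". That is a separate matter. What counts here is that 0.23 SD refers to a difference between groups at follow-up, which is not the contrast in the model sentence.

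**Step 3: how large the bias could be (illustration)**

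Two inputs are assumed and are not in the document: a baseline gap g of 0.1 to 0.2 SD between the chosen groups, and a pre-post correlation r of 0.6. The true effect is set to zero.

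*Unadjusted comparison of follow-up means, gap regressing to the mean.* Bias = r × g:
- 0.6 × 0.1 = 0.06 SD, and 0.06 / 0.23 = 26% of the detectable difference.
- 0.6 × 0.2 = 0.12 SD, and 0.12 / 0.23 = 52%.
- In standard errors: 0.06 / 0.0929 = 0.65 and 0.12 / 0.0929 = 1.29. A nominal two-sided 5% test then rejects in about 10% and 25% of cases.

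*Group-by-time (change) contrast without covariates.*
- Stable gap: bias = 0.
- Gap regressing to the mean: bias = -(1 - r) × g, that is -0.4 × 0.1 = -0.04 SD and -0.4 × 0.2 = -0.08 SD. The sign is opposite to the follow-up comparison.

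*Baseline as a covariate.*
- Gap regressing to the mean: bias = 0.
- Stable gap: what remains is g - r × g, that is 0.1 - 0.06 = 0.04 SD and 0.2 - 0.12 = 0.08 SD.

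Neither way of handling baseline is unbiased under both assumptions. One should be named as primary and the other kept as a sensitivity analysis.

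**The case against.** **A group comparison is plainly intended.** The abstract applies the same regressions to the difference between groups, the design is described as controlled, and the interaction sentence presupposes an effect of the intervention. This stands. A reader might infer from the model sentence that only a pooled time change will be tested, but read as a whole the document does not support that. The sentence is misstated and needs reconciling.

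**The model sentence includes T0, so a follow-up-only comparison is not what it describes.** This also stands. The 0.06 to 0.12 SD belongs to an analysis the article neither states nor excludes. For a change contrast the bias is smaller, of opposite sign, and zero if the gap is stable. A reader might infer that confounding would be as large as the 0.23 SD effect; the figures under these assumptions do not reach that.

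**Site is balanced.** Each site plans 120 participants per arm, so disease group does not confound the pooled comparison by design, and analyses are repeated by site. This stands. Site belongs in the model for precision and to guard against unequal attrition.

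**Some stronger statements go beyond the text.** The article calls the listed variables likely modifiers of the effect, not confounders. It does not say that the professionals who recruit know the group of their patients. Both would be inferences.

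**Covariate lists are often left to the analysis plan.** This stands in part. An unseen plan may specify adjustment, and silence alone would be no finding. But the article states a contrast that conflicts with its own objective, and it gives these variables only a role that does not control confounding.

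**Conclusion.** The point holds in a limited form. The model sentence in Data management and analyses does not match the contrast in the abstract, objectives, hypotheses and power calculation. No part of the article yields a confounder-adjusted group effect in a study whose groups are not randomised. The conclusion rests on the wording and needs no numerical assumption.

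The size is illustrative only. It depends on the assumed gap and correlation, and on which unadjusted analysis would be run: 0.06 to 0.12 SD for follow-up means, and between 0 and -0.08 SD for change, against 0.23 SD. The direction of any actual bias cannot be told from the document.

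**What to change.** Reword the model sentence before outcome data are analysed:

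- The main estimate is the intervention-control difference at T1, and at T2, from the multilevel model.
- Adjust it for age, sex, living situation and education, and include site.
- Handle baseline in one stated way: either as a covariate with T1 and T2 as outcomes, or with T0 as an outcome and group-by-time terms, but not both in one model. Report the other as a sensitivity analysis, because the groups are not equivalent.
- Use the same covariates in the logistic models.
- Keep the interaction tests as secondary analyses.

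The cost is a change of wording and a little more analysis work. The covariates already feature in the planned subgroup analyses. Some records will be lost, or need imputation, where a covariate is missing.
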